### 10.3 Relationship to Investigational Product

The relationship of an AE or serious adverse event (SAE) is assessed and determined by the Principal Investigator or designee. All medically indicated and available diagnostic methods (e.g., lab, blood smear, culture, X-ray, etc.) should be used to assess the nature and cause of the AE/SAE. Best clinical and scientific judgment should be used to assess relationship of AE/SAEs to the investigational product and/or other cause.

The following should be considered for the assessment of relationship of adverse events to the investigational product:

- Presence/absence of a clear temporal (time) sequence between administration of the investigational product and the onset of AE/SAE
- Presence/absence of another cause that could more likely explain the AE/SAE (concurrent disease, concomitant medication, environmental or toxic factors, etc.)
- Whether or not the AE/SAE follows a known response pattern associated with the investigational product

*The relationship assessment should be reported as one of the following:*

**Not Related:** clearly explained by another cause (concurrent disease, concomitant medication, environmental or toxic factors, etc.).

**Unlikely:** more likely explained by another cause (concurrent disease, concomitant medication, environmental or toxic factors, etc.).

**Possibly:** equally likely explained by another cause but the possibility of the investigational product relationship cannot be ruled out (e.g., reasonably well temporally related and/or follows a known investigational product response pattern but equally well explained by another cause).

**Probably:** more likely explained by the investigational product (e.g., reasonably well temporally related and/or follows a known investigational product response pattern and less likely explained by another cause).

**Definitely:** clearly related and most likely explained by the investigational product

For the purpose of expedited safety reporting, all possibly, probably or definitely related SAEs are considered investigational product related SAEs.

#### 10.4 Serious Adverse Events

*An adverse event is reported as a "Serious Adverse Event" if it meets any the following criteria (as per ICH GCP Guidelines):*

- Results in death
- Is life threatening
- Results in persistent or significant disability/incapacity.
- Requires in-patient hospitalization or prolongs existing hospitalization.
- Is a congenital anomaly/birth defect or spontaneous abortion.
- Any other important medical condition that requires medical or surgical intervention to prevent permanent impairment of a body function or structure.

SAEs must be reported to IAVI within 24 hours of the research centre becoming aware of the event. All SAEs must be reported using the designated SAE Report Form and sent to the sponsor according to SAE Reporting Guidelines (see Study Operations Manual).

To discuss investigational product related SAEs or any urgent medical questions related to the SAE, the research centre investigator should contact one of the IAVI medical monitors directly (see the Contact List).

The IAVI SAE Report Form should be completed with all the available information at the time of reporting. The minimum data required in reporting an SAE are the volunteer identification number, date of birth, gender, event description (in as much detail as is known at the time), onset date of event (if available), reason event is classified as Serious, reporting source (name of principal investigator or designee), relationship assessment to the investigational product by the investigator.

The Principal Investigator or designee is required to write a detailed written report with follow up until resolution or until it is judged by the principal investigator or designee to have stabilized.

The Principal Investigator or designee must notify the local IRB/IEC of all SAEs as appropriate. In case of investigational product related SAEs, the sponsor and/or the investigational product provider will notify local regulatory authorities, Safety Review Board and other study research centres where the same investigational product is being tested.

More details on SAE definitions and reporting requirements are provided in the SAE Reporting Guidelines (see Study Operations Manual).

## **10.5 Clinical Management of Adverse Events**

Adverse events (AEs) will be managed by the clinical study team who will assess and treat the volunteer as appropriate, including referral. If any treatment/medical care is required as a result of the harm caused by the investigational product or study procedures, this care will be provided free of charge.

If a volunteer has an adverse event and/or abnormal laboratory value that is known while the volunteer is taking the investigational product, the specifications of Section 12.0 will be followed.

Volunteers will be followed until the adverse event resolves or stabilizes or up to the end of the study, whichever comes last. If at the end of the study, an adverse event (including clinically significant lab abnormality) that is considered possibly, probably or definitely related to the investigational product is unresolved, follow-up will continue until resolution if possible and the volunteer will be referred.

## **10.6 Pregnancy**

Although not considered an adverse event, if a female volunteer becomes pregnant during the study, it is the responsibility of the Principal Investigator or designee to report the pregnancy promptly to IAVI using the designated forms. However, serious complications of pregnancy that meet SAE criteria specified in the Section 10.4 of this Protocol (e.g., eclampsia, spontaneous abortion, etc.) should be reported as SAEs.

If a female volunteer becomes pregnant during the study, the administration of the investigational product will be discontinued and the volunteer followed until the end of pregnancy. Approximately 2–4 weeks after delivery, the baby will be examined by a physician to assess its health status and the results will be reported to IAVI.

## **10.7 Intercurrent HIV Infection**

If a volunteer is found to be HIV-infected through exposure in the community, the administration of the investigational product must be discontinued and the volunteer followed according to procedures described in Section 12.2.

Intercurrent HIV infection in study volunteers, although not considered an SAE must be reported promptly to IAVI using the designated forms. However, serious medical conditions associated with the HIV infection that meet SAE criteria specified in the Section 10.4 of this Protocol (e.g., sepsis, PCP pneumonia, etc.) should be reported as SAEs using SAE Report Form.

## **11.0 MANAGEMENT OF HIV ISSUES DURING AND FOLLOWING STUDY**

### **11.1 HIV Testing**

Volunteers will be tested for HIV-1 and HIV-2 antibodies as indicated in the Schedule of Procedures (Appendix A1) or as needed, if medical or social circumstances arise. Frequent HIV testing is an important component of this protocol, so investigational product will be stopped immediately after HIV infection is detected. This process may help avoid the risk of developing drug resistant viral mutations.

All volunteers will receive HIV prevention counselling and pre-HIV-test and post-HIV-test counselling as specified in Section 11.2.

### **11.2 HIV infection**

Volunteers who are found to be HIV infected at screening and volunteers who acquire HIV infection during the study will be provided the following:

#### **11.2.1 Counselling**

The volunteer will be counselled by the study counsellors. The counselling process will assist the volunteer with the following issues:

- Psychological and social implications of HIV infection
- Whom to inform and what to say
- Implications for sexual partners
- Implications for child-bearing
- Avoidance of transmission to others in future

#### **11.2.2 Referral for Support and/or Care**

Volunteers will be referred to a patient support centre or institution of his/her choice for a full discussion of the clinical aspects of HIV infection. Referral will be made to a designated physician or centre for discussion of options of treatment of HIV-infection.

For those individuals who become HIV infected after enrolment in the study, antiretroviral therapy will be provided when clinically indicated according to accepted treatment guidelines. If not available through another program, antiretroviral therapy will be provided at no charge for up to 5 years after treatment is initiated.

HIV-infected pregnant women will be referred for prenatal care and to a program for the Prevention of Mother to Child Transmission (PMTCT). The pregnant volunteer will be followed according to timeline as specified in Section 10.6.

#### **11.2.3 Follow-up of HIV-Infected Volunteers**

If a volunteer becomes HIV-infected during the study, they will be followed for an additional two visits as detailed in Appendix A1 to collect blood to characterize the infection, including CD4+ T cell count, HIV viral

load, p24 antigen and other assays for early seroconversion and virus detection, Western Blot, HIV genotyping for drug-resistance mutations, viral tropism assays, HIV sequencing and other testing to characterize the infection. The volunteer will not participate in any other E002 visits, including the Final Visit / Week 24 Visit. Then the volunteer will be offered enrollment into a separate long-term follow-up protocol to follow their HIV infection.

## 12.0 **DISCONTINUATION OF ADMINISTRATION OF INVESTIGATIONAL PRODUCT AND/OR WITHDRAWAL FROM STUDY**

### 12.1 **Discontinuation of administration of investigational product**

Any volunteer discontinuing from investigational product or being considered for discontinuation of investigational product will be discussed with the sponsor. Volunteers will be discontinued from investigational product for any of the following reasons:

1. Pregnancy
2. Intercurrent HIV infection
3. A disease or condition or an adverse event that may develop, regardless of relationship to the investigational product, if the principal investigator or designee is of the opinion that further investigational product is not in the best interest of the volunteer.
4. Use of antiretroviral medications or other medications that may interact with investigational product
5. Volunteer request to discontinue further participation.
6. Participating in another clinical study of an investigational product
7. Creatinine clearance (CrCl)  $\leq 50$  mL/min, as calculated by Cockcroft-Gault formula
8. Any of the other following abnormal laboratory parameters that occur after randomization:

#### **For all laboratory values except creatinine elevations:**

##### Grade 1 or 2

Continue study medication at the discretion of the study physician.

##### Grade 3 or 4

May continue study medication for up to 3 days while values are confirmed

##### Confirmed Grade 3

- If unrelated or unlikely related to study drug by above definitions, may continue dosing
- If causal relationship to study drug possible by above definitions (e.g., possibly, probably, or definitely related), withhold drug until toxicity returns to  $<$  grade 3 then restart study drug
- If toxicity  $\geq$  grade 3 recurs, permanently discontinue dosing follow as frequently as clinically indicated (up to study closure) until toxicity resolves

Confirmed Grade 4

Permanently discontinue study drug  
Follow as frequently as clinically indicated (up to study closure) until toxicity resolves

**Serum Creatinine Elevation**

All Grades

Continue study medication for up to 3 days while values are confirmed

Confirmed Grade 1

Continue study medication at the discretion of the study physician  
Monitor weekly until return to within 0.3 mg/dL of the baseline value

Confirmed Grade 2-4

Permanently discontinue study drug  
Monitor as clinically indicated (generally at least monthly up to 3 months) until return to within 0.3 mg/dL of the baseline value

**12.2. Follow Up After Discontinuation of Further Administration of Investigational Product**

Volunteers, in whom further administration of investigational product are discontinued due to adverse events, will be followed until the adverse event resolves or stabilizes or up to the end of the study, whichever comes last. These volunteers will not participate in the Final Visit / Week 24 Visit. Volunteers who are discontinued for any reason will not be replaced.

HIV infected individuals who have received investigational product will be followed for an additional two visits after discontinuing investigational product to assess for the development of drug resistance mutations. If drug resistance is detected and determined to be related to study participation, further follow-up will be determined by the Safety Review Board.

Follow-up of pregnant volunteers will be done as specified in Section 10.6.

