#### *Study Population*

The participating research centre in Masaka, Uganda has extensive experience working with HIV-discordant couples. HIV negative individuals living in HIV discordant relationship are a potentially appropriate population in which to evaluate intermittent PrEP. Discordant couples are one of the highest risk groups for HIV infection. In Uganda, the incidence is estimated to be about 4-5 per 100 person years, higher than in Uganda general adult population (1-2 per 100 person years) [165]. In addition, intermittent PrEP may be desirable for couples if sexual activity is sporadic or in couples where childbearing is desired. The MRC Uganda has experience in recruiting and enrolling discordant couples in observational and interventional research. A longitudinal study of HIV discordant couples was initiated in Masaka in 2005 as part of a multi-centre effort to prepare for HIV vaccine efficacy trials. The cohort study currently follows approximately 500 discordant couples near Masaka with quarterly follow-up. The observed annual HIV incidence is 4.0 (95% CI 2.6 –5.5) [MRC unpublished data].

*Relationship between adherence, plasma drug levels and intracellular drug levels*  
A critical determinant of PrEP efficacy will be how varying adherence behavior

causes varying drug levels over time. There is substantial variation in pharmacokinetics between individuals. The combination of daily MEMS adherence data combined with an individual's peak-trough drug levels (plasma and intracellular), after an observed dose (enhanced with population-based estimates), provide a relatively more precise estimation of drug concentration at any point in time. Such a longitudinal pharmacokinetic model based on observed drug levels and daily adherence behavior can reveal specific periods of subtherapeutic drug exposure that places individuals at risk for HIV transmission. After achieving steady state, specimens for plasma and intracellular drug levels will be collected at the Week 4 visit. Serum will be collected immediately prior to a scheduled witnessed dose to determine  $C_{min}$  and again approximately 2 hours and 24 hours after a witnessed dose to determine  $C_{max}$ . This will establish the typical range of drug plasma concentrations in each volunteer defined by the peak-trough relationship.

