### **6.3 Post-randomization Visits for HIV-uninfected volunteers**

The volunteer will be asked to return to the clinic on the days specified in Appendix A1. Procedures will be conducted at these visits as specified in Appendix A1.

During these visits, routine safety laboratory parameters from the previous visit will be reviewed. If a volunteer had an abnormal laboratory value, specified guidelines (Section 12.0) will be followed.

HIV pre-test counselling will be conducted if an HIV test is required (Appendix A1) and post-test counselling will be provided if the results of a prior HIV test are given to the volunteer.

At the Week 4 visit only, a single-dose timed pharmacokinetic study will be conducted. In addition to the procedures listed above, the following procedures will be conducted:

- To reduce the variability in test results, volunteers will be asked to eat a standard meal
- After eating, collection of blood specimen for plasma and intracellular drug levels
- Witnessed dosing of investigational product immediately after specimen collection
- Repeat collection of blood specimen approximately 2 hours after dosing
- Repeat collection of blood specimen approximately 24 hours after dosing

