## **6.7 Final Visit**

After stopping study drug at week 16 (see section 6.5), volunteers will have one additional follow-up visit at week 24, to assess for undetected HIV infection and immune responses once off study drug.

Research centre personnel will:

- Conduct HIV pre-test counselling or provide post-test counselling if the results of a prior HIV test are being provided to the volunteer.
- Collect blood and specimens for tests as specified in the Schedule of Procedures (Appendix A).
- Conduct HIV post-test counselling
- Provide HIV risk reduction counselling

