#### **7.12 Randomization and Blinding**

Volunteers will be identified by a unique volunteer identification number.

The randomization schedule(s) will be prepared by the statisticians at the Data Coordinating Center (DCC) prior to the start of the study. Volunteers will be assigned a specific allocation number. An unblinding list will be provided to the research centre by the DCC for use in case of medical emergency as described below.

This study is double-blinded. Research centre personnel (investigator and clinical personnel monitoring the safety and laboratory assay results) and volunteers will be blinded with respect to the allocation of investigational product (placebo or FTC/TDF) but dosing regimen, daily or intermittent, will not be blinded.

Volunteers will be informed about their group assignment once the database is locked. If a study volunteer is unblinded and becomes aware of treatment group assignment, further administration of the investigational product (FTC/TDF or placebo) will be discontinued. The study volunteer will be followed up until the end of the study.

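### Volunteers who stop drug for an adverse event are barred from Week 24, so those stopping after about Week 8 miss the 8-week off-drug HIV test and immune sample that completers get

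*Protocol*

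**What the plan says.** Section 12.2 of the protocol makes two statements about volunteers whose drug is stopped for an adverse event. They "will be followed until the adverse event resolves or stabilizes or up to the end of the study, whichever comes last". The next sentence adds: "These volunteers will not participate in the Final Visit / Week 24 Visit".

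Section 6.7 places the Final Visit at Week 24, after dosing ends at Week 16, "to assess for undetected HIV infection and immune responses once off study drug". Appendix A1 schedules an HIV test and a PBMC sample at Weeks 4, 8, 12, 16 (or early termination) and 24.

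Other volunteers who stop drug are handled differently. After unblinding, section 7.12 says: "The study volunteer will be followed up until the end of the study". For volunteers who become infected, section 11.2.3 says "they will be followed for an additional two visits as detailed in Appendix A1"; that section also takes them out of Week 24.

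The adverse-event ground in section 12.1 applies "regardless of relationship to the investigational product", so the exclusion is not confined to drug-related events.

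**The concern.** The first sentence in section 12.2 can be read as follow-up of the adverse event only, so the two sentences need not contradict each other. On that reading, though, no off-drug HIV test or immune sample is planned at Week 24 for these volunteers, and nothing else in the protocol requires one:

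- The two extra visits in sections 11.2.3 and 12.2 are for volunteers already known to be infected. They characterise an infection and do not look for an undetected one.
- The early termination visit (section 12.4) is triggered by withdrawal from the study, not by stopping drug.
- Section 11.1 allows further HIV tests as circumstances require, and section 5.2.7 lets volunteers stay in the parent cohort study. Neither is required for this purpose.

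The people affected have taken study product, are HIV-uninfected as far as is known, and were enrolled because they have an HIV-infected partner not on ART.

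The statistical point is that the Week 24 sample becomes missing by rule, after a post-randomization event that active drug may cause. Section 14.2 calls for modified intention-to-treat analysis, and section 14.2.8 counts a volunteer as an immune responder on any one positive test. Fewer samples mean fewer chances to be counted. Ascertainment could therefore differ between arms, although the protocol has no stopping rates from which to show that it would.

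**Working it through.** **1. Time off drug at the last scheduled HIV test (section 6.7, Appendix A1)**

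Completers: 24 − 16 = 8 weeks.

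A volunteer who stops at week *s*, is barred from Week 24 and keeps the visits to Week 16: 16 − *s* weeks.

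| Stop week | Weeks off drug at Week 16 | Shortfall against 8 weeks |
|---|---|---|
| 4 | 12 | 0 |
| 8 | 8 | 0 |
| 10 | 6 | 2 |
| 12 | 4 | 4 |
| 14 | 2 | 6 |

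The break-even is a stop at Week 8. Section 12.2 does not say whether the Week 12 and Week 16 visits continue. If they do not, the loss is wider.

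One route into the affected window is a Week 8 chemistry result. Section 6.3 says that at visits "routine safety laboratory parameters from the previous visit will be reviewed", so a stop based on that result could come anywhere between Week 8 and the Week 12 review, leaving 8 down to 4 weeks off drug at Week 16.

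**2. Expected infections in the untested 8 weeks**

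Inputs: section 3.7 (Study Population) says "The observed annual HIV incidence is 4.0" per 100 person-years, with 95% interval 2.6 to 5.5. The number of stops is not given, so 1 to 5 is assumed.

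Per volunteer:
- 0.026 × 8/52 = 0.0040
- 0.040 × 8/52 = 0.0062
- 0.055 × 8/52 = 0.0085

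Range: 1 × 0.0040 = 0.004 to 5 × 0.0085 = 0.042. This counts infections acquired between Weeks 16 and 24. It does not count any acquired earlier and still undetected at Week 16.

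**3. Effect on the immune comparison**

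The plan's own figure comes first. Section 14.2.8 assumes 10% against 50%, with 24 volunteers per group (section 14.1). Exact enumeration of Fisher's test, two-sided 0.05 (assumed, as the section states neither), gives 83.4%, against the stated 83%.

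Now assume five independent post-baseline samples (Weeks 4, 8, 12, 16, 24) with a cumulative response of 50%:
- per-sample positivity: 1 − 0.5^(1/5) = 12.9%
- response over four samples: 1 − (1 − 0.129)^4 = 42.6%
- arm rate with *k* of 24 barred: [(24 − *k*) × 50% + *k* × 42.6%]/24

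| *k* | Arm rate | Power |
|---|---|---|
| 0 | 50.0% | 83.4% |
| 1 | 49.7% | 82.9% |
| 3 | 49.1% | 81.7% |
| 5 | 48.5% | 80.5% |

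**4. With the exclusion removed**

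Anyone who stops at or before Week 16 has 24 − *s* ≥ 8 weeks off drug at Week 24, and the planned 83.4% is unchanged.

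**The case against.** **Few volunteers fall in the window.** Scheduled chemistry and haematology are drawn at Weeks 4, 8 and 16, and section 12.1 allows about three days of dosing while an abnormal result is confirmed. A promptly handled Week 8 stop then leaves nearly 8 weeks off drug at Week 16. The 4-week end of the example requires the result to wait for the Week 12 review. This stands: the group is mainly clinical or unscheduled stops between Weeks 8 and 16. It reduces the number affected but does not empty the window.

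**Eight weeks is not a stated requirement.** The protocol sets no minimum off-drug interval, and a Week 12 or Week 14 stop still has an off-drug test at Week 16. This also stands. What is lost is the equivalent of the completers' sample, not every off-drug sample.

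**Infected volunteers miss Week 24 too.** True, but they have a known diagnosis and two dedicated visits. The adverse-event group has no such replacement, and no reason for its exclusion is given.

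**Testing may happen elsewhere.** As-needed tests or parent-cohort visits could fill part of the gap. They might, but the plan does not rely on them for this.

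**The power figures rest on an assumption.** The study summary in section 3.7 speaks of two to three immune time points, and samples from one person are unlikely to be independent. Fewer time points would enlarge the modelled loss and within-person correlation would shrink it. A different illustration, with 1 to 3 late stops and 10% to 50% of responders positive only at Week 24, gives power from about 83% down to 77.3%. These figures show scale only. Immune response is listed under other endpoints (section 5.1.2), and section 9.2.2 describes the evaluations as exploratory.

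**Conclusion.** The concern holds as a minor, inexpensive improvement. The exclusion is explicit, it removes the visit set up for the off-drug HIV check and immune sample, and nothing required by the protocol replaces it. It matters for volunteers who stop for an adverse event after about Week 8. Those who stop by Week 8 lose little, provided they keep the Week 12 and Week 16 visits.

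The numerical effect is small, and it rests on an assumed 1 to 5 stops and, for power, on independent samples. An imbalance between arms is possible but not shown. No stated figure is wrong, and earlier samples, the analysis cohort and the primary endpoints are untouched. The case for change is each volunteer's off-drug HIV check and consistent follow-up after stopping drug, rather than power.

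**What to change.** Delete the sentence in section 12.2 that keeps these volunteers out of Week 24. HIV-uninfected volunteers who stop drug for an adverse event would then attend, if they consent, for the HIV test and immune samples already listed in Appendix A1. Report Week 24 attendance by arm and by reason for non-attendance.

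The cost is one deleted sentence and a few additional volunteer visits of a type already scheduled.
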